#### Pulse oximetry

All physicians will be asked to measure pulse oximetry by means of a paediatric finger pulse oximeter (CMS50QA, Contec™ Medical Systems, China), provided for this trial, measuring oxygen saturation and pulse rate. A small-scale pilot study was performed to determine the appropriate age requirements for the device (above 3 years of age) and agreement with a large-size pulse oximeter.

### Outcome measures

#### Primary outcome measure

Serious infections, defined as a hospital admission for more than 24 hours for any of these diagnoses:Sepsis (including bacteraemia) with a pathogenic bacteria isolated from a haemoculture as the reference standardMeningitis (viral or bacterial) with a positive lumbar puncture (pleocytosis in cerebrospinal fluid and identification of a bacteria or a virus) as the reference standardAbscess with a positive culture as the reference standardPneumonia (viral or bacterial) with an infiltrate seen on chest x-ray as the reference standardOsteomyelitis (pathogens from bone aspirate as the reference standard, or if unavailable with a MRI or bone scan suggestive for osteomyelitis)Cellulitis (acute suppurative inflammation of the subcutaneous tissues)Gastro-enteritis with dehydrationComplicated urinary tract infection (positive urine culture (>10^5^/ml pathogens of a single species) and systemic effects such as fever)Viral respiratory tract infections complicated by hypoxia (e.g. bronchiolitis)

If a serious infection occurs within 10 days after inclusion, it will be considered a consequence of the same illness episode. To ensure a firm definition of the outcome (a serious infection), the outcome will be measured through three strategies: (I) a thorough search of each child’s electronic medical record at the hospitals within the referral region of the participating FP or paediatrician, (II) the results from interviewing the physician who included the child in the study, and finally (III) the results from the diary filled out by parents after consulting the FP, mentioning the date the child is no longer ill.

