## Abstract

**Background:**

Acute illness is the most common presentation of children to ambulatory care. In contrast, serious infections are rare and often present at an early stage. To avoid complications or death, early recognition and adequate referral are essential. In a recent large study children were included prospectively to construct a symptom-based decision tree with a sensitivity and negative predictive value of nearly 100%. To reduce the number of false positives, point-of-care tests might be useful, providing an immediate result at bedside. The most probable candidate is C-reactive protein, as well as a pulse oximetry.

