**Methods:**

This is a diagnostic accuracy study of signs, symptoms and point-of-care tests for serious infections. Acutely ill children presenting to a family physician or paediatrician will be included consecutively in Flanders, Belgium. Children testing positive on the decision tree will get a point-of-care C-reactive protein test. Children testing negative will randomly either receive a point-of-care C-reactive protein test or usual care. The outcome of interest is hospital admission more than 24 hours with a serious infection within 10 days. Aiming to include over 6500 children, we will report the diagnostic accuracy of the decision tree (+/− the point-of-care C-reactive protein test or pulse oximetry) in sensitivity, specificity, positive and negative likelihood ratios, and positive and negative predictive values. New diagnostic algorithms will be constructed through classification and regression tree and multiple logistic regression analysis.

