## Background

Acute illness is the most common reason for encounter of children attending ambulatory care.

In a primary care setting, less than 1% of children assessed will have a serious illness [1]. The incidence of serious infections in children is assumed to be 5 to 10 times higher at the paediatric emergency department [2]. Febrile illness accounts for 20% of all paediatric ED visits [3].

Serious infections are rare in children in developed countries, but associated with considerable morbidity and mortality [4]. In Flanders, infectious diseases are responsible for 8.0% of all deaths in children under the age of one year, and for 13.6% of deaths in children aged 1 to 14 years [1, 5]. These numbers are comparable to death rates previously reported in the UK [6]. Serious infections in children are usually defined as sepsis, meningitis, pneumonia, pyelonephritis, gastroenteritis with dehydration, osteomyelitis, complicated abscess, viral respiratory infection with hypoxia, and cellulitis [7]. The mortality of meningococcal disease can be as high as 25% [8]. Besides this, approximately 7% of children who survive bacterial meningitis suffer from hearing loss [9].

Serious infections need to be distinguished from the vast majority of self-limiting viral conditions in children. Those few children with a serious infection can present at an early stage when the severity of the infection is not yet apparent [4]. At that point, their symptoms tend to mimic those of children with a non-serious illness. The rapid deterioration could cause a diagnosis to be missed at first contact, sometimes with severe consequences. Early recognition and adequate referral of serious infections are of vital importance to avoid complications. A faster and more accurate recognition of serious diseases could prevent unnecessary investigations, referrals, treatments and hospitalisations in children without serious illness, avoiding traumatic experiences for the child, parental concerns and health care expenditures.

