## Methods

### Design

This is a prospective diagnostic accuracy study in ambulatory care (defined as general practice, paediatric outpatient clinics or emergency departments) identifying the diagnostic value of signs, symptoms and technological tests in diagnosing serious infections using hospital admission more than 24 hours for a serious infection as the main outcome measure (Figure 1).

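### The primary outcome has no death component, so a child who dies of a listed infection before admission or within 24 hours of it is classed as not having a serious infection

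*Protocol article*

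**What the plan says.** The Primary outcome measure section gives the definition: "Serious infections, defined as a hospital admission for more than 24 hours for any of these diagnoses", followed by nine diagnoses, several with a required reference standard (for example a positive blood culture for sepsis, a positive lumbar puncture for meningitis, an infiltrate on chest x-ray for pneumonia). Two other places agree with it. The abstract has "The outcome of interest is hospital admission more than 24 hours with a serious infection within 10 days", and the Design section describes the study as "using hospital admission more than 24 hours for a serious infection as the main outcome measure".

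The same section sets the time window, "If a serious infection occurs within 10 days after inclusion, it will be considered a consequence of the same illness episode", and states that "the outcome will be measured through three strategies": hospital records, an interview with the including physician, and the parents' diary. These say when and how the outcome is looked for. They do not add to what counts as the outcome.

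Death appears only in the rationale. The abstract opens with "To avoid complications or death, early recognition and adequate referral are essential". The Background section says "The mortality of meningococcal disease can be as high as 25" per cent and, on early presentation, "The rapid deterioration could cause a diagnosis to be missed at first contact, sometimes with severe consequences".

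**The concern.** The rule makes case status depend on staying in hospital for more than 24 hours. A child with fulminant infection who dies sooner, or never reaches hospital, cannot satisfy it. No other category is provided, and the Statistical analysis section reports sensitivity, specificity, likelihood ratios and predictive values, so that child goes into the non-diseased column.

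The direction of the error matters. If the tree had been negative, a missed fatal infection is scored as correct reassurance. Sensitivity and negative predictive value are the two properties for which the article cites values near 100% from the derivation study and which this study sets out to validate. The rule therefore favours the tree in the situation that the rationale describes as the one to prevent. If the tree had been positive, a correct alarm is scored as a false positive.

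**Working it through.** **1. Follow one child through the rule.** Take a child with a listed infection who dies within 10 days of inclusion.

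| Course | Stay over 24 hours? | Status as written | Tree negative | Tree positive |
|---|---|---|---|---|
| Dies after more than 24 hours in hospital | yes | case | false negative | true positive |
| Dies within 24 hours of admission | no | non-case | true negative | false positive |
| Dies in the emergency department or at home | no | non-case | true negative | false positive |

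The first row is handled correctly, provided that the reference standard is met. The gap is confined to the other two.

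**2. Reproduce the plan's figures.** The Sample size section assumes a sensitivity of 97% and a minimal lower confidence limit of 85%, and arrives at 59 cases. It states neither the sidedness of the limit nor the probability of meeting it. I searched for the smallest n at which the exact (Clopper-Pearson) lower limit is at least 85% with the required probability when the true sensitivity is 97%.
- One-sided 95% limit, probability 95%: n = 59, with at least 55 of 59 detected (probability 0.968). This matches.
- Two-sided 95% limit: n = 46, 56 and 66 for probabilities of 80%, 90% and 95%.
- Controls = 59 × (1 − p)/p: 7316 at p = 0.8% and 6497 at p = 0.9%. Both match.
- Expected cases among 6500 children: 6500 × 0.008 = 52 and 6500 × 0.009 = 58.5.

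**3. Illustrate the effect on sensitivity.** The expected number detected is 0.97 × 59 = 57.2, so start from 57 of 59. Let k be the number of tree-negative early deaths; k is an assumption, because the article gives no rate. Counted as cases, they give a sensitivity of 57/(59 + k). The lower limit is the α quantile of Beta(57, 3 + k), with α = 0.025 (two-sided) or 0.05 (one-sided).

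| k | Sensitivity | Lower limit, two-sided 95% | Lower limit, one-sided 95% |
|---|---|---|---|
| 0 (as the rule would report) | 57/59 = 96.6% | 88.3% | 89.7% |
| 1 | 57/60 = 95.0% | 86.1% | 87.6% |
| 2 | 57/61 = 93.4% | 84.1% | 85.6% |
| 3 | 57/62 = 91.9% | 82.2% | 83.8% |

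**4. Tree-positive early deaths.** If two such deaths were tree-positive, sensitivity would be 59/61 = 96.7% against 57/59 = 96.6%, which is practically no change. Under the present rule they would be two extra false positives.

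**5. Negative predictive value.** The number of tree-negative children, N, is not known in advance, but the relative change does not depend on it. With 2 false negatives the missed fraction is 2/N. One reclassified death makes it 3/N (half as much again) and two make it 4/N (double). The absolute change is tiny if N is in the thousands.

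**The case against.** Admission for more than 24 hours is a deliberate outcome choice, and the numerical case is weak. The article gives no rate of death before admission or within 24 hours. The 25% for meningococcal disease is an upper figure for one disease and is not tied to early death. If early deaths were missed at the planned 3% (an assumption), two missed deaths would imply about 2/0.03 = 67 early deaths, more than all planned cases. With three early deaths in the cohort, the chance that at least two were tree-negative is 3 × 0.03² × 0.97 + 0.03³ = 0.3%, or 10% at a 20% miss rate. This stands as a limit on size. It does not make the rule correct.

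A reader might infer three stronger points, none of which the article supports.
- *One or two records decide whether the study succeeds.* The 85% is a planning value in the Sample size section. The Statistical analysis section reports estimates with 95% intervals and sets no pass mark. On the one-sided limit that reproduces 59 cases, two missed deaths leave the limit at 85.6%; three are needed to go below 85%.
- *Children transferred within 24 hours are misclassified too.* The text does not restart the clock at a second hospital, and it searches the records of all hospitals in the referral region. At most this is an ambiguity.
- *One added sentence and the three existing sources settle it.* A child who dies early may have no culture, lumbar puncture or imaging, and so would still fail several reference standards. According to the Implementation section, only parents of children seen by a family physician fill in the diary.

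**Conclusion.** The point holds as a flaw in a stated definition. The outcome is fixed in the same terms in three places, has no death clause, and by its own wording puts early deaths from a listed infection among the non-cases. The article never says outright that such children are controls; this follows from the definition and the two-by-two analysis.

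For tree-negative children the bias has one direction, upward in sensitivity and negative predictive value. Its size is unknown and may be zero. The illustration (about 1.6 percentage points of sensitivity for each of the first two missed deaths) assumes 57 of 59 detected and deaths that were tree-negative. The sample size is not affected. The reason to act is that the correction is cheap and the gravest possible failure of the tree should not be scored as a success. The full protocol is not shown and may deal with this, but the outcome as stated here does not.

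**What to change.** Define the primary outcome as admission for more than 24 hours for any of the listed diagnoses, or death within 10 days of inclusion attributed to any of them, whatever the length of stay. Carry the same wording into the abstract and the Design section.

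Add a rule for cause of death: where culture, lumbar puncture or imaging is not available, cause is assigned from the hospital record and the physician interview by assessors who do not know the tree and CRP results. The interview should ask explicitly whether the child died, since for a death outside hospital it may be the main source. The consent wording should be checked as well, because the article describes record access in terms of a possible admission.

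The cost is a few sentences, one interview item and a judgement on cause of death in very few children. That judgement is less firm than a laboratory standard, so report the number of cases that entered by this route and show sensitivity with and without them.

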#### Secondary outcome measure

Use of other diagnostic tests and medical services (including re-consultation).

### Sample size

Based on the binomial distribution, at an expected sensitivity of 97% with a minimal acceptable lower confidence limit of 85%, the minimal number of cases is 59, not taking into account the non-monotonic nature of power as a function of sample size due to discreteness of the binomial distribution [24]. The number of controls, derived through the formula N_controls_ = N_cases_ [(1-Prevalence)/Prevalence], [25] is 7316 at a prevalence of 0.8% and 6497 at a prevalence of 0.9%.

Considering the sample size calculation, we aimed to include 6500 children (in 88 general practices and 12 paediatric units), across Flanders, in urban and rural areas over a period of 12 months.

### Implementation

#### Recruitment of physicians

We will compose a letter with a short description of the research and the (dis)advantages of participating, with the option to request further information. This letter will be distributed by email to all FPs known to the research partners trough personal and professional contacts. Interested family physicians (FPs) will be contacted and visited by the researchers to inform them more extensively about the trial. Participating FPs will complete a short questionnaire about practice characteristics. For more details about this questionnaire, we refer to Lemiengre et al. [22]. After agreement to participate, all physicians will be visited and instructed on the inclusion process. At this point in time, we will inform the FPs about their allocation by the investigator. The step-by-step plan will be explained in detail. All FPs will get a demonstration to properly perform the POC CRP test.

We will ask the paediatricians involved in the project steering committee and their colleagues affiliated with a university hospital to participate in the study and include eligible children at the outpatient clinic, as well as the emergency department. We’ll ask them to contact other interested colleagues affiliated with hospitals across Flanders, with a workload of acutely ill children similar or higher compared to the university hospitals. After agreement to participate, a meeting with all participating paediatricians will be organised to explain the trial in detail. All paediatricians will get a demonstration to perform the POC CRP test.

Parents will be informed through posters in the waiting room, as well as flyers, with a short comprehensible description of the background, aims and requirements to participate. Physicians will inform every eligible child and their parent(s), delivering an information leaflet and asking formally to participate. Parents and children from the age of 12 will sign a written informed consent form, with a permission to access the hospital medical record in case of a possible admission. We will provide adjusted information leaflets and consent forms for minors below and above 12 years of age.

We will ask physicians to perform a thorough history taking and physical examination of every child, registering items based on experience from previous research and clinical consensus of an international team of clinicians and researchers, [26] such as measurement of the NICE traffic light system, the Yale Observation Scale, the 5-stage decision tree, and vital signs, such as a pulse oximetry [27–29].

The clinician will record the gathered data, preliminary diagnosis and planned actions (e.g. investigations, treatment or referral) on a case report form. Only parents of children attending a FP’s office will complete a booklet, containing 4 surveys and a follow up diary. For more details about this booklet and the related procedures, we refer to Lemiengre et al. [22].

We will ask parents to send a text message to the investigators on the day the child is no longer sick. These children will automatically enter a prize draw and prices will be awarded monthly amongst these children.

#### Follow-up

We intend to contact physicians at least on a monthly basis, via email, telephone or regular mail, as well as use occasional motivational gifts to remind them of this trial and encourage consecutive inclusions. A gift-savings system for physicians will be introduced with children toys for the doctor’s waiting room.

If a physician is clearly not including children or violating the in- or exclusion criteria of this study, the trial will be discontinued in this practice and replaced by a new motivated practice willing to participate, with similar practice type and region.

### Ethics

The protocol of this study was approved by the Ethical Review Board of the University Hospitals/KU Leuven, under reference ML8601. All children’s parents are requested to provide written informed consent. As soon as all hospitals within the referral region of all participating FPs are known, these centres will be submitted for formal approval by the coordinating and the local ethical review boards.

## Discussion

Feverish illness is the most common reason for encounter of children attending ambulatory care. In contrast, serious infections are rare in children in developed countries, but associated with considerable morbidity and mortality.

Those few children with a SI can present at an early stage when the severity of the infection is not yet apparent. A faster and more accurate recognition of serious diseases could prevent unnecessary investigations, referrals, treatments and hospitalisations in children without serious illness. On the other hand, children with apparent signs of a life-threatening serious infection should immediately be referred to or seen at the ED or an urgent-access paediatric clinic. Unnecessary delay of adequate treatment and management decisions should be avoided in these children.

Signs and symptoms are the first information to support clinical decision making in primary care [30]. Parental concern is an important predictor of SI, as well as the clinician’s feeling that “something is wrong” (gut feeling) [10]. Other red flags, such as cyanosis, rapid breathing, poor peripheral circulation, meningeal irritation and petechial rash have been shown to increase the likelihood of a serious infection in ill children [4].

Blood tests are only rarely performed in acutely ill children in primary care, due to the need to make management decisions prior to the availability of test results. Very little research has been performed in ambulatory care and none of it in primary care specifically. However, a role has been put out for CRP and procalcitonin to rule out serious infections [15].

POC tests enable physicians to adjust their management according to the immediate test results. They are minimally invasive, and thus relevant in paediatric care.

Research is needed to further inform clinicians and parents. Triage, face-to-face assessment in primary care, as well as evaluating clinical features, laboratory tests and safety netting, needs to be further examined [30].

To our knowledge, this is the first large-scale trial, investigating the (added) value of POC CRP in addition to clinical features in identifying serious infections in acutely ill children in ambulatory care, including general practice, paediatric outpatient clinics and hospital emergency departments.

## Abbreviations

SI: Serious infections
POC: Point-of-care
CRP: C-reactive protein
PCT: Procalcitonin
FP: Family physician
ED: Emergency department
ROC: Receiver operating characteristic.
